## Abstract

**Background:**

Pain is common in the first 2 days after major craniotomy. Inadequate analgesia may lead to an increased risk of postoperative complications. Most pain following craniotomy arises from the pericranial muscles and soft tissues of the scalp. Scalp nerve blocks with local anesthesia seem to provide effective, safe, however, transient postoperative analgesia which does not seem to meet the requirements of craniotomy. Currently, peripheral dexamethasone has been observed to significantly prolong the duration of analgesia of nerve blocks (e.g., saphenous nerve block, adductor canal block, thoracic paravertebral block, brachial plexus nerve block). On the contrary, a study reported that perineural dexamethasone did not appear to prolong the analgesic time after supratentorial craniotomy. However, all patients in this study were given 24 mg of oral or intravenous dexamethasone regularly for at least 7 days during the perioperative period, which possibly masked the role of single local low doses of perineural dexamethasone. Therefore, the analgesic effect of single dexamethasone for scalp nerve blocks without the background of perioperative glucocorticoid deserves further clarification.

**Methods:**

The REDUCE trial is a prospective, single-center, parallel-group randomized controlled trial involving a total of 156 adults scheduled for elective craniotomy with general anesthesia. Patients will be randomly divided among two groups: the control group (*n* = 78) will receive scalp nerve blocks with 0.5% bupivacaine, plus normal saline with epinephrine at 1:200,000; the DEX_4mg_ group (*n* = 78) will receive scalp nerve blocks with 0.5% bupivacaine, plus 4 mg dexamethasone with epinephrine at 1:200,000. The primary outcome will be the duration of analgesia, defined as the time between the performance of the block and the first analgesic request.

**Discussion:**

The REDUCE trial aims to further assess the analgesic effect of single dexamethasone as an adjuvant to scalp nerve blocks for relief of postcraniotomy pain without the background of perioperative glucocorticoid.

**Trial registration:**

ClinicalTrials.govNCT04648358. Registered on November 30, 2020.

**Supplementary Information:**

The online version contains supplementary material available at 10.1186/s13063-021-05747-y.

## Administrative information

Note: the numbers in curly brackets in this protocol refer to SPIRIT checklist item numbers. The order of the items has been modified to group similar items (see http://www.equator-network.org/reporting-guidelines/spirit-2013-statement-defining-standard-protocol-items-for-clinical-trials/).

## Introduction

### Background and rationale {6a}

Pain is often considered an inevitable outcome of surgery. Postcraniotomy patients have frequently been assumed to experience modest pain among all surgeries. However, current evidence suggests that pain after neurosurgical procedures is more severe than expected [1, 2]. A prospective study of 187 patients demonstrated that pain was common in the first 2 days after major craniotomy, with approximately 70% of patients reporting moderate to severe pain during the 1st postoperative day and 48% of patients complaining of pain scores greater than or equal to 4 on the 2nd postoperative day [2]. Sympathetically mediated hypertension caused by inadequate analgesia may lead to an increased risk of postoperative complications, such as arterial hypertension, intracranial hemorrhage, prolonged hospital stays, and mortality [3]. In addition, undertreated acute postoperative pain may predict the development of chronic pain [4–6]. Therefore, optimal pain management is of great importance for improving postoperative recovery and patient comfort [7].

Opioids are commonly used for postoperative analgesia, but the use of opioids for neurosurgical procedures is limited by potential side effects such as sedation, miosis, nausea, vomiting, and respiratory depression [8]. Multimodal analgesic techniques, such as combining an opioid with supplemental analgesics (including nonsteroidal anti-inflammatory drugs (NSAIDs), scalp infiltration, and scalp nerve blocks), typically result in improved analgesia with concurrent reductions in the incidence of systemic opioid-related adverse effects [8, 9]. The neural tissue of the brain does not contain any pain receptors. Most pain following craniotomy arises from the pericranial muscles and soft tissues of the scalp [10]. Therefore, scalp nerve blocks, which suspend the function of the sensory nerve fibers in the superficial and deep soft tissue layers, can reduce the consumption of analgesic drugs and may enhance early postoperative recovery.

Scalp nerve block is a widespread technique that has been utilized in anesthetic and neurosurgical practice for several decades. Scalp nerve blocks with local anesthetics seem to enable effective and safe anesthetic management and are also critical for awake craniotomy procedures [11–13]. In neurosurgery, scalp nerve blocks can be performed by directly blocking several different nerves such as the supraorbital and supratrochlear nerves, the auriculotemporal nerves, the zygomaticotemporal nerves and the greater, lesser, and third occipital nerves that provide sensory innervation of the scalp in neurosurgery [14]. Lee et al. suggested that 0.25% bupivacaine scalp nerve blocks could effectively attenuate the hemodynamic response to skin incision and dural opening in patients undergoing craniotomy with general anesthesia [15]. There was also evidence that the pain intensity was reduced after scalp nerve blocks with local anesthetics in the first few hours after craniotomy [16–19]. Even with adrenaline used as an additive agent, scalp nerve blocks using 0.5% or 0.75% bupivacaine with adrenaline improved postoperative analgesia for a maximum of only 6 h after craniotomy [20, 21]. On the contrary, Rigamonti et al. revealed that scalp nerve blocks with 0.5% bupivacaine with adrenaline did not decrease the severity of postoperative pain for patients undergoing supratentorial craniotomy [22]. Therefore, to meet the analgesic requirements of craniotomy, improving the quality and prolonging the duration of scalp nerve blocks is of great significance. Continuous perineural catheter is a common technique to prolong the effect of local anesthetics. However, there are potential risks with these catheters themselves (e.g., dislocation, prolonged motor block, infection) [23–25]. Adjuvants have been used to prolong the duration of postoperative analgesia to avoid these defects. Among the different adjuvants, the potent long-acting glucocorticoid agonist dexamethasone is one of the most acceptable adjuvants.

In 2003, Shrestha et al. firstly reported that peripheral dexamethasone significantly prolonged the duration of analgesia of brachial plexus block [26]. Subsequently, the addition of dexamethasone (1~8 mg) was observed to prolong the median duration of analgesia by 27~39% in various nerve blocks (e.g., saphenous nerve block, adductor canal block, thoracic paravertebral block, brachial plexus nerve block) without any unwanted effects [27–36]. Among them, a meta-analysis of optimal dose of perineural dexamethasone suggested that 4 mg of perineural dexamethasone represents an analgesic ceiling dose and higher doses failed to provide additional analgesic duration [34]. The possible mechanisms of perineural dexamethasone prolonging the analgesic time of the peripheral nerve block are by reducing local anesthetics absorption by inducing a degree of vasoconstriction [37] and decreasing activity of C fibers by inhibiting potassium channels [38]. Moreover, there is no evidence of significant neurotoxicity of perineural administration of dexamethasone [39]. On the contrary, in a pioneering study, Jose et al. applied 8 mg dexamethasone as an adjuvant to 0.2% ropivacaine for scalp nerve blocks and reported that perineural dexamethasone did not appear to prolong the analgesic time after supratentorial craniotomy. However, all patients were given 24 mg of oral or intravenous dexamethasone regularly at least 7 days during the perioperative period. Such persistent high doses of systemic dexamethasone possibly masked the role of single local low doses of perineural dexamethasone. The analgesic effect of single dexamethasone for scalp nerve blocks without the background of perioperative glucocorticoid deserves further clarification.

We postulate that without the background of perioperative glucocorticoid, the use of single dexamethasone as an adjuvant to scalp nerve blocks can prolong the analgesic duration, reduce opioid consumption and improve the quality of scalp nerve blocks compared with bupivacaine alone after supratentorial craniotomy. The primary outcome will be the duration of analgesia, defined as the time between the performance of the block and the first analgesic request.

### Objectives {7}

We aim to assess the effectiveness of scalp nerve blocks with local anesthetics plus dexamethasone for the relief of postcraniotomy pain without the background of perioperative glucocorticoid.

### Trial design {8}

This study is a prospective, single-center, parallel-group randomized controlled, superiority trial. The planned study has been registered at ClinicalTrials.gov under the identifier NCT04648358. See Fig. 1 for the flow chart. Additional File 1 shows the Standard Protocol Items: Recommendations for Interventional Trials (SPIRIT) checklist for study protocols.

**Fig. 1 Fig1:**
[figure not shown]
Flow chart of the study procedure. DEX, dexamethasone; NRS, Numeric Rating Scale; GCS, Glasgow Coma Scale score; PACU, postoperative care unit; PONV, postoperative nausea and vomiting

## Methods: Participants, interventions, and outcomes

### Study setting {9}

A high-volume center with broad expertise in neurosurgery will be involved in enrollment (Beijing Tiantan Hospital, Capital Medical University). Recruitment of patients for the REDUCE trial started in December 2020, and the trial is expected to complete in 2022.

### Eligibility criteria {10}

#### Inclusion criteria

Patients scheduled for elective supratentorial craniotomy under general anesthesia will be consecutively screened for eligibility based on the following criteria: age 18 to 64 years; an American Society of Anesthesiologists (ASA) physical status of I, II or III; and a preoperative Glasgow Coma Scale (GCS) score of 15/15. Each participant must be able to understand the nature and potential individual consequences of the clinical trial.

#### Exclusion criteria

History of chronic headache or chronic pain syndrome of any cause, psychiatric disorders or uncontrolled epilepsy;Inability to understand or use the pain scales before surgery;Excessive alcohol or drug abuse, chronic opioid use (more than 2 weeks or 3 days per week for more than 1 month), use of drugs with confirmed or suspected sedative or analgesic effects, or use of any painkiller within 24 h before surgery;Request of oral/intravenous glucocorticoid to decrease cerebral edema within 1 week before surgery;Pregnancy or breastfeeding;Extreme body mass index (BMI) (< 15 or > 35);Participation in another interventional trial that interferes with the intervention or outcome of this trial;Refusal or inability of the patient and/or legal guardian to provide informed consent;Coagulopathy;Infection around the puncture site; andHistory of allergies to any of the study drugs.

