#### Subject withdrawal criteria

Subjects may withdraw from the study under the following circumstances: subjects cannot complete this trial, or they request, for various reasons, that they not be subjected to the intervention; oral/intravenous glucocorticoid is required to decrease cerebral edema intraoperatively or postoperatively; the planned craniotomy is not performed; or adverse events (AEs) force subjects to withdraw from the trial. Subjects who withdraw will be included in the final report of the REDUCE trial to ensure full transparency.

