### Criteria for discontinuing or modifying allocated interventions {11b}

Prior to providing consent, it will be explained that participation in this clinical trial is voluntary and that each participant has the right to withdraw from the study at any time, without stating reasons, without incurring disadvantages for their future care or benefits. Participants can withdraw from the study at their own request or at the principal investigator’s (PI) discretion. Withdrawal of consent can result in the termination of patient’s participation. No further study-related measures will be carried out. The PI will be responsible for any amendment of the trial. Any protocol amendment will be submitted by PI and approved by the Institutional Review Board (IRB).

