### Relevant concomitant care permitted or prohibited during the trial {11d}

On arrival to the postanesthesia care unit (PACU) or intensive care unit (ICU), each patient will receive patient-controlled analgesia (PCA) pumps including 100 μg sufentanil and 16 mg ondansetron diluted to 100 mL of 0.9% saline. Postoperatively, when the patient reports a numeric rating scale (NRS) score of 4 or more, or at the request of the patient, patients will be treated with PCA 2 μg bolus, with a lockout interval of 10 min, without continuous background infusion dose or loading dose, and a maximum of 8 μg per hour. The type and doses of postoperative analgesic supplementation will be recorded in detail in the case report form (CRF).

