### Provisions for post-trial care {30}

All types of AEs that occur from the day of randomization to the end of follow-up will be reported to the sponsor as soon as possible after the research staff identifies the event. Meanwhile, patients will also be treated as soon as possible if any AEs occur during the trial. The drug combinations, such as the drug name, frequency of use, dosage form, and dose, will be recorded in detail by researchers.

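### The steroid exclusion covers only glucocorticoid given for cerebral edema, while the objective assumes no perioperative glucocorticoid at all (minor)

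*Protocol article*

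**What the plan says.** The Objectives section sets the question as the effect of the block plus dexamethasone "for the relief of postcraniotomy pain without the background of perioperative glucocorticoid". The hypothesis at the end of Background and rationale uses the same condition. Neither names an indication for the steroid. The reason given is an earlier scalp-block study in which all patients received 24 mg dexamethasone for at least 7 days: "Such persistent high doses of systemic dexamethasone possibly masked the role of single local low doses of perineural dexamethasone".

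Two rules name steroids, and both are limited by purpose:

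- Exclusion criteria: "Request of oral/intravenous glucocorticoid to decrease cerebral edema within 1 week before surgery".
- Subject withdrawal criteria: patients may be withdrawn if "oral/intravenous glucocorticoid is required to decrease cerebral edema intraoperatively or postoperatively".

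Some other text bears on the point without naming a steroid rule:

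- The Exclusion criteria also list "use of drugs with confirmed or suspected sedative or analgesic effects".
- Section 11b leaves withdrawal partly to judgement: "Participants can withdraw from the study at their own request or at the principal investigator’s (PI) discretion".
- Section 11d covers concomitant care and says only "The type and doses of postoperative analgesic supplementation will be recorded in detail in the case report form (CRF".
- The Anesthesia protocol has intraoperative drug doses recorded.
- Section 30, in a paragraph on adverse events, adds "The drug combinations, such as the drug name, frequency of use, dosage form, and dose, will be recorded in detail by researchers".

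**The concern.** The condition that separates this trial from the earlier negative study is the absence of background glucocorticoid. The argument for that condition rests on drug, dose and duration. Why the steroid was prescribed plays no part in it. Limiting the exclusion to one indication therefore does not follow from the rationale: a patient on systemic glucocorticoid for some other illness meets the written criteria yet may carry the very background the trial sets out to remove.

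At stake is the match between the enrolled population and the stated question. If such patients respond less to the perineural dose, the estimated difference shrinks a little. Allocation is randomized and assessment blinded, so preoperative use should be similar across arms in expectation, and no bias towards either arm is expected.

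**Working it through.** **Comparing the texts.** Objective and hypothesis: no perioperative glucocorticoid, any indication. Exclusion: oral or intravenous, for edema, 1 week before surgery. Withdrawal: oral or intravenous, for edema, during or after surgery. The uncovered set is systemic glucocorticoid for any other indication. The Discussion names one such use, prophylaxis of nausea and vomiting, but the trial's own antiemetic is ondansetron (8 mg after surgery, 16 mg in the PCA pump). Routine antiemetic dexamethasone is therefore not counted here.

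**The plan's own sample size.** From Sample size: control mean 600 min, SD 240 min, effect 30% of 600 = 180 min, 90% power, α 0.05, minimal important difference 60 min.

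- Plain two-sided test: n = 2 × 240² × (1.960 + 1.282)² / 180² = 37.4, so 38 per group (39 by t test). This is not 70.
- One-sided 0.05 test of superiority by a 60 min margin: n = 2 × 240² × (1.645 + 1.282)² / (180 − 60)² = 68.5, so 69 (70 by t test). This reproduces 70.
- Dropout: 70 / 0.9 = 77.8, so 78 per group and 156 in total.

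The Statistical methods section specifies 2-tailed group comparisons and no margin, so the calculations below use the plain two-sided test with 70 per group.

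**Dilution.** Let f be the share of both arms on non-edema systemic steroid. The article gives no value, so f is an assumption. Power is from the noncentral t with 138 degrees of freedom, critical value 1.977 and noncentrality Δ / (240 × √(2/70)) = Δ / 40.57.

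| f | No effect in exposed: Δ = 180(1 − f) | Power | Half effect in exposed: Δ = 180(1 − f/2) | Power |
|---|---|---|---|---|
| 0 | 180 | 99.3% | 180 | 99.3% |
| 2% | 176.4 | 99.1% | – | – |
| 5% | 171 | 98.7% | 175.5 | 99.0% |
| 10% | 162 | 97.8% | 171 | 98.7% |
| 20% | 144 | 94.1% | 162 | 97.8% |

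In patients, 5% of 156 is 7.8 (about 8) and 10% is 15.6 (about 16).

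**Break-even.** The difference detectable with 90% power at 70 per group is 132.4 min, so f = 1 − 132.4/180 = 26%.

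**Cost of a sensitivity analysis without exposed patients.** With the full 180 min and n = 70(1 − f) rounded down: 66 per group at 5% (99.0%), 63 at 10% (98.7%) and 56 at 20% (97.6%).

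**The case against.** The strongest reply is that the background in question is the regimen of the earlier study, 24 mg for at least 7 days, and not every steroid exposure. On that reading a patient on a low or replacement dose is not outside the objective. This is a fair reading, and such doses may dilute little or not at all. But the objective as written carries no such limit, and the edema clause does not supply one: it restricts by purpose and leaves dose open, so a high dose for another indication also passes.

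A second reply is that cover exists. Edema is plausibly the main indication, and ondansetron takes the antiemetic role. The clause on analgesic or sedative drugs could be read to include dexamethasone, and the principal investigator may withdraw a patient. Each point reduces the number of patients affected. None is a steroid rule: the drug clause does not name steroids, and since steroids have their own item, two screeners could reasonably apply it differently.

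A third reply is that recording detail and extra analyses belong to the case report form, the full protocol or the analysis plan. That is right as far as it goes: the absence of a steroid provision in section 11d is not itself a fault, and details of the per-protocol set are left to the analysis plan. The eligibility wording is different, because the article states it, and an analysis plan cannot widen an exclusion.

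Lastly, the calculated effect is tiny. That stands, and it is why the point is minor.

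**Conclusion.** The point holds as a minor mismatch: the steroid exclusion is narrower than the condition in the objective and hypothesis. Confidence in the wording gap is high. Its practical size is not known from the article, because no rate of non-edema steroid use is given. Under the upper-bound assumption that exposed patients gain nothing, 5% exposure takes 9 min off a 180 min effect and 10% takes off 18 min. Power with the plain two-sided test remains well above the planned 90%. The expected consequence is slight dilution with no favoured direction, and no loss of planned power.

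This rests on the 180 min effect, the SD of 240 min, equal exposure in both arms and the two-sided test in Statistical methods. If the 60 min margin test that reproduces 70 per group were really intended, there would be no surplus. In the same worst case power would go from 90.3% to 85.9% at 5% (difference over the margin 171 − 60 = 111 min) and to 80.4% at 10% (162 − 60 = 102 min). The article states no such test, so the rating does not rest on it.

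**What to change.** Replace the exclusion item with: any systemic glucocorticoid, for any indication, within 1 week before surgery. Leave the withdrawal rule as it is, since widening it would add withdrawals after randomization.

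In support:

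- Record any non-study systemic glucocorticoid from surgery to 48 h, with drug, dose, time and indication.
- Keep exposed patients in follow-up and in the modified ITT analysis.
- Add one sensitivity analysis that excludes patients exposed for any indication, using chart data for those already enrolled. Treat it as supportive only, because postoperative exposure arises after randomization.

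The eligibility change is worth making even if the recording item and the sensitivity analysis are handled in the case report form and the analysis plan.

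The sample size does not change. Intraoperative doses are already recorded, so the extra work is checking the preoperative week and confirming steroid use to 48 h. The costs are a few more screen failures (including some low-dose patients who might have diluted nothing) and a chart check for those already in the trial. Eligibility would also differ slightly before and after the amendment, because recruitment began in December 2020 and changes apply only to subsequent patients.

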#### Subject withdrawal criteria

Subjects may withdraw from the study under the following circumstances: subjects cannot complete this trial, or they request, for various reasons, that they not be subjected to the intervention; oral/intravenous glucocorticoid is required to decrease cerebral edema intraoperatively or postoperatively; the planned craniotomy is not performed; or adverse events (AEs) force subjects to withdraw from the trial. Subjects who withdraw will be included in the final report of the REDUCE trial to ensure full transparency.

### Who will take informed consent {26a}

Patients who want to take part in the study can communicate with the study coordinator to learn more about the study. A study coordinator will explain the rationale and methodology of the study face to face to the patient or legal representative. The patient or legal representative has the option to ask questions and the opportunity to consider whether to participate in this trial. If the patient is willing, consent will be obtained for the REDUCE trial. Then, written informed consent documents will be securely locked in one place.

